### **5.3. Type of control and study design**

This study is a phase IV-II study.

The study design will be multicentre, comparative, randomised, double-blind and parallel, with two arms. It is designed to evaluate, in the first part, the separate effects of *Plantago ovata* husk, and in cases where the therapeutic objective is not attained, the combined action of this fibre and a statin (20 mg of simvastatin) in adults with several cardiovascular risk factors will be studied (see figure 1).

Figure 1. *Plantago ovata* Study design

[figure not shown]

#### **5.4. Run-in periods**

The study includes an initial run-in period S-2(D-15) in which the patients will be given an appointment to ascertain whether they comply with the inclusion/exclusion criteria, they will be informed about the study characteristics and will also be asked to provide two blood samples, to be taken on days D-10 ( $\pm 2$ ) and D-7 ( $\pm 2$ ). Mainly, these two analyses are aimed at determining the patients' baseline LDL-C value. If it is within the margins established as an inclusion criterion, the patient will be informed of this at visit S0 and will be randomised.

### **6. SELECTION OF STUDY POPULATION**

All men and women aged above 20 years, with an LDL cholesterol higher than or equal to 130 mg/dl and lower than or equal to 189 mg/dl will be invited to participate in the study. These patients must have at least 1 cardiovascular risk factor.

The following are regarded as risk factors:

- \* Age above 45 years in men and above 55 years in women,
- \* Smoker
- \* High blood pressure
- \* HDL-C  $\leq 40$  mg/dl in men and  $\leq 46$  mg/dl in women
- \* Family background of early heart disease

#### **6.1. Inclusion criteria**

1. Levels of LDL-C between  $>130$  mg/dl and  $<189$  mg/dl
2. Present at least 1 of the cardiovascular risk factor defined in the preceding section.
3. Be capable of following diet guidelines
4. Patients who have given informed consent.

#### **6.2. Exclusion criteria**

1. Triglycerides  $>350$  mg/dl (threshold that allows to determine LDL-C according to the Friedewald's formula).
2. Chronic alcoholism.
3. BMI  $>35$  kg/m^2
4. History of cardiovascular disease.
5. Treatment with statins prior to the beginning of the trial and who have not dropped out at least 2 months before the beginning of the study.
6. Have diabetes mellitus (at least 2 glycemias, in fasting, above 126 mg/dl).
7. Renal disease (creatinine plasma levels  $> 124$   $\mu$ mol/l (1.4 mg/dl) for women and  $> 133$   $\mu$ mol/l (1.5 mg/dl) for men.
8. Have acute infectious diseases, neoplasms, severe liver failure, chronic respiratory failure or associated endocrine diseases.

9. Other conditions, such as special nutritional requirements or medications that may affect lipid metabolism or blood pressure.
10. Participate or have participated in a clinical trial in the last 3 months.
11. Incapacity to follow the study.
12. Allergy to *Plantago ovata*.
13. History of gastrointestinal disease that may alter the absorption of nutrients.
14. Intestinal obstruction or pseudo obstruction.
15. Depression syndrome or self-injuring ideation.

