### 6.3. Sample size

#### Total sample: 290 patients (145 per group)

The results of an earlier study by Sprecher 1993, measuring the effect of 10.2 g of *Plantago ovata* a day in the reduction of the levels of LDL cholesterol were used to calculate the sample.

The value of the effect to be detected ( $d = 7.5$  mg/dl) is equivalent to a reduction of 5% of LDL in patients with LDL baseline values of 150 mg/dl.

The working hypothesis is:

$$H_0: \Delta \text{LDL } \textit{plantago ovata} - \Delta \text{LDL placebo} < |7.5| \text{ mg/dl}$$

$$H_1: \Delta \text{LDL } \textit{plantago ovata} - \Delta \text{LDL placebo} \geq |7.5| \text{ mg/dl}$$

Where  $\Delta \text{LDL} = \text{final LDL} - \text{baseline LDL}$

For a statistical significance of  $\alpha = 0.05$  and a power of 80%, with a standard deviation of 20 mg/dl in the  $\Delta \text{LDL}$ , the sample size required to detect significant differences of 7.5 mg/dl between the group treated with *Plantago ovata* and the group treated with placebo is 112 patients per group, for which, adjusted to an expected percentage of losses of 15%, a total of **270 patients** will be required.

After treatment, approximately 75% of the patients treated with soluble fibre (84 patients) and 85% of those treated with placebo (95) will not have 130 mg/dl of LDL-C in plasma. A statin will be added to all these patients' treatment.

It is assumed that the combination of soluble fibre with statins will cause the mean value of LDL-C to fall from 157 mg/dl to 125.6 mg/dl ( $\Delta \text{LDL}$  soluble fibre + statin = 31.4 mg/dl). In the placebo + statin group from 161 mg/dl to 136.85 mg/dl ( $\Delta \text{LDL}$  placebo+statin = 24.15 mg/dl).

For a statistical significance of ( $\alpha=0.05$ ), a power of 80%, a standard deviation in the  $\Delta \text{LDL}$  of 18.5 mg/dL and a ratio of 0.85 between groups treated with placebo for 0.75 treated with soluble fibre, **the sample size** necessary to detect differences of

7.25 mg/dl in the  $\Delta$ LDL between the group treated with statin+soluble fibre and the group treated with statin + placebo is 111 patients in the placebo group and 98 patients in the soluble fibre group.

As the percentage of failure in the objective of LDL-C equal to or lower than 130 mg/dl is 75% in the patients treated with soluble fibre and 85% in those treated with placebo, adding a 10% of patients lost to follow-up means that a **total sample of 290 patients (145 per group)** will be required.

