
#### **6.4. *Interim analysis and interruption criteria***

The study withdrawal criteria will be:

- The presence of serious adverse events that lead patients to stop taking the product.
- The appearance of a serious disease with hospitalisation criteria.
- The taking of drugs other than those described as permitted.
- Non-compliance with the diet, defined by the following criteria:
  - energy provided by lipids more than 40%.
  - energy provided by saturated fatty acids higher than 15%.
- Non-compliance with fibre treatment. Compliance below 80% will be grounds for withdrawal.

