### 7.2.2 Prohibited treatments

- Statins (during the first 8-week period)
- Resins
- Fibrates
- Nicotinic acid and derivatives
- Ezetimibe
- Anticoagulants
- Minerals and vitamins
- Digoxin

It should be emphasised that patients may have followed some of the prohibited treatments for up to a minimum period of two months before their inclusion in the study.

All the drugs that the volunteer may take must be recorded.

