#### ➤ Clinical

Contact will have been made with all the possible participants from the centres for the systematic control of people in whom hypercholesterolemia has been detected. Similarly, patients from the lipid clinic of each centre will have been contacted.

Contact will be by a letter and/or by telephone call explaining the detailed contents on the **Patient Information Sheet**. (Annex 3)

Patients who agree to participate in the study will be invited to this initial visit to confirm that they meet the selection criteria. They will be given the patient information sheet and they will be invited to sign the informed consent form (Annex 4) for their participation in the trial.

At this visit a detailed clinical history will be made, particularly with regard to:

- Age
- Smoking
- Intake of alcohol
- Blood pressure
- Background of cardiovascular disease
- Concomitant diseases: diabetes mellitus, renal failure, serious acute infectious diseases, neoplasm, severe liver failure, chronic respiratory failure or associated endocrine diseases.
- Concomitant pharmacological treatments.
- Physical activity.
- The patient's diet

The physical activity of each participant will be assessed according to a specific questionnaire (Annex 5).

The physical examination will include the determination of blood pressure, weight, height, BMI and waist size.

The participant's weight will be determined: on one occasion the patient will get off the scales and will then be reweighed; the mean value of the 2 weighings will be calculated.

The height of the patient will be measured in the following way: the subject will breathe in and the height meter will be lowered to determine height. The measurement will be repeated and the mean value of the 2 measurements will be calculated.

Patients that comply with the selection criteria will be given the Patient Information Sheet and will be asked to **sign the Informed Consent Form** (Annex 4) to participate in the trial.

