#### ➤ *Clinical*

A clinical history similar to that of S-2 will be made to confirm compliance with the inclusion criteria

Blood pressure and weight and height will be measured to calculate BMI at the physical examination.

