**Visit S4 (Day 28± 3)**

The participants will go to the Hospital and the visit will comprise several aspects:

➤ *Clinical*

Identify the presence of clinical problems, concomitant treatments, etc.  
Collection of adverse events

Blood pressure and weight will be taken.

➤ *Analytical*

A request for two analyses will be issued. For the blood extractions, the patient will go to the hospital during the week prior to visit S8 on two occasions, with a 3- or 4-day interval between them, and the last extraction will be performed at most 3 days before the following visit. In this way, the investigator will have both results, particularly for the lipid profile, at the S8 day visit.

Only the lipid profile will be determined at the first extraction. At the second extraction, and besides the lipid profile, the same biochemistry and haematological parameters as at visit S0 will be requested. Genetic polymorphisms will not be determined.

➤ *Dietary*

The patient will return the diet record delivered at week S0.

A new 3-day diet record to be returned at the following visit will be provided. (S8).

➤ *Medication*

Evaluate compliance with treatment with fibre. The patient should return used and unused medication containers.

The investigator will deliver the medication for the following treatment period until the next visit in week 8.

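### Pregnancy and breast-feeding appear in no entry, withdrawal or visit rule, and no stated rule stops treatment for a pregnancy that begins before simvastatin is added at S8

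*Protocol*

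**What the plan says.** **Who may enter.** Section 6 invites "All men and women aged above 20 years" whose LDL-C is in range and who have at least one of five risk factors. One is age (above 55 in women). The others are smoking, high blood pressure, low HDL-C and a family history. Section 6.1 does not narrow this.

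**Who may not.** Section 6.2 has 15 exclusion criteria. The nearest to the present point is number 9: "Other conditions, such as special nutritional requirements or medications that may affect lipid metabolism or blood pressure".

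**Who is withdrawn.** Section 6.4 has five criteria: certain serious adverse events, serious disease needing hospital care, "The taking of drugs other than those described as permitted", diet non-compliance and fibre compliance below 80%.

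**What is asked at visits.** The S-2 history in section 8.2 names nine topics, one of them beginning "Concomitant diseases: diabetes mellitus, renal failure, serious acute infectious diseases, neoplasm, severe liver failure". At S0, "A clinical history similar to that of S-2 will be made to confirm compliance with the inclusion criteria". The S8 history follows the S0 one. From S4 onwards each clinic visit has the item "Identify the presence of clinical problems, concomitant treatments, etc".

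**What happens at S8.** LDL-C below 130 mg/dl ends participation. LDL-C of 130 mg/dl or more means simvastatin 20 mg/day is added for 8 weeks.

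**Rules during treatment.** Section 7.2.2 prohibits "Minerals and vitamins". Section 8.3.2 sets an isocaloric diet to hold weight steady, with energy intake changed once weight moves by more than 1 kg.

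**The concern.** The protocol admits women who could be pregnant or breast-feeding, or could become pregnant during the 16 weeks, but its operative rules never mention either state. The gap is widest after entry. A second drug starts two months after the eligibility check, when a woman's status may have changed, and the stated decision rule looks at LDL-C.

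The trial's other rules would apply to her without exception: no vitamins or minerals, and a diet managed to keep weight constant. What is at stake is participant safety and consistent handling across centres, because each investigator would have to decide alone whether to exclude, continue or stop. The estimate of the LDL-C effect is not at stake.

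**Working it through.** This is a reading of the text, with a little arithmetic for scale.

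**1. Can a younger woman qualify?** Yes. One risk factor is enough, and four of the five are unrelated to age.

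**2. Is either condition named?**

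| Place | Items | Naming pregnancy or breast-feeding |
|---|---|---|
| 6.2 exclusion criteria | 15 | 0 |
| 6.4 withdrawal criteria | 5 | 0 |
| 8.2 S-2 history topics | 9 | 0 |
| Annex 1 rows | 19 | 0 |

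The listed items for S0, S4, S8, S12 and S16 in 8.2 do not name them either, and Annex 1 has no pregnancy test. Section 9.3 counts a birth defect as a serious adverse event, but that concerns reporting an outcome, not preventing exposure.

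**3. What cover is there at entry?** Exclusion 9 is mandatory where it applies, and its wording can be read to include pregnancy and lactation. The S-2 history is described as detailed, with particular attention to the nine topics, so they are not a closed list. A dietician also works out energy needs from a 3-day record before S0. This is real but unnamed cover.

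**4. What cover is there after entry?** The visits look for clinical problems, and a non-permitted drug leads to withdrawal. Neither makes pregnancy itself a reason to stop. A woman who began a vitamin supplement would be withdrawn for the supplement. One who kept to the rules would meet no stated reason to stop.

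**5. Who does the S8 rule reach?** Section 6.3 expects that "approximately 75% of the patients treated with soluble fibre (84 patients) and 85% of those treated with placebo (95") will miss the target, and says all of them receive a statin. Those counts reproduce on the 112 per group of the first-phase calculation:

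- fibre: 0.75 × 112 = 84
- placebo: 0.85 × 112 = 95.2, stated as 95

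On the planned 145 per group, before losses:

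- fibre: 0.75 × 145 = 108.75
- placebo: 0.85 × 145 = 123.25
- together: 232.0 of 290, or 80%

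With the 10% loss that 6.3 allows: 0.90 × 232 = 208.8, about 209. These rates are for all patients, not for women who could be pregnant.

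**6. Exposure per woman.** Up to 16 weeks of blinded product, issued at S0, S4, S8 and S12 (4 visits). Up to 8 weeks of simvastatin, issued at S8 and S12 (2 visits).

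**7. How many women?** The protocol gives no age or sex distribution, so this cannot be calculated. Any count would only restate whatever shares and rates were assumed.

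**The case against.** The best defence is that silence in these lists is not absence of protection. Exclusion 9 binds the investigator and plausibly covers both states at entry. The history is open-ended. The S8 visit includes a history, a search for clinical problems and collection of adverse events, so LDL-C is not the only thing looked at that day. Weighing at every visit could bring a pregnancy to notice. The ban on supplements, combined with the withdrawal rule, would itself remove some women. All of this stands, and it is why the point is limited to cover that is partial at entry and unstated afterwards.

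Two stronger readings are tempting but unsupported:

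- A reader might infer that nobody in the trial has to ask about pregnancy. The documents do not show that. The case report form is attached separately, and the patient information sheet, the consent form and part of section 9 were not available for this review. Any of them may contain such a question or instruction.
- A reader might infer that the protocol gives a drug it knows to be unsafe in pregnancy. Nothing in the visible text says that simvastatin or the fibre is contraindicated then, so the point does not rest on that.

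The unseen documents do not remove the point. Eligibility and withdrawal rules belong in 6.2 and 6.4, which are fully visible, and a question on a form does not tell the investigator to stop treatment.

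**Conclusion.** The point holds in this limited form. Women above 20 can enter on factors unrelated to age, and no exclusion, withdrawal criterion, listed visit item or Annex 1 row names pregnancy or breast-feeding. Entry is partly covered by a general criterion and an open history. After entry no stated rule stops treatment for pregnancy, and LDL-C of 130 mg/dl or more is the only stated criterion for adding simvastatin in patients who continue.

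Per woman the possible exposure is up to 16 weeks of blinded product and 8 weeks of simvastatin. The number affected is not derivable and probably small, and the primary LDL-C result is not touched. It should be changed because it concerns safety and costs almost nothing. The textual absence is certain. Practice at the sites may already be better than the text, since the case report form and consent documents could not be checked.

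**What to change.** First check whether the case report form and consent documents already deal with pregnancy, and confirm that section 9 contains a rule for reporting one. Then:

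- add pregnancy and breast-feeding as a named exclusion in 6.2
- add pregnancy as a named withdrawal criterion in 6.4
- in 8.2, ask and record pregnancy status in the existing S0 and S8 histories before any medication is issued

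The cost is wording in three sections and, if not already present, one case report form item. Slightly fewer women will be eligible, and two existing visits each gain one question. No sample-size or analysis change is needed.

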### 6.3. Sample size

#### Total sample: 290 patients (145 per group)

The results of an earlier study by Sprecher 1993, measuring the effect of 10.2 g of *Plantago ovata* a day in the reduction of the levels of LDL cholesterol were used to calculate the sample.

The value of the effect to be detected ( $d = 7.5$  mg/dl) is equivalent to a reduction of 5% of LDL in patients with LDL baseline values of 150 mg/dl.

The working hypothesis is:

$$H_0: \Delta \text{LDL } \textit{plantago ovata} - \Delta \text{LDL placebo} < |7.5| \text{ mg/dl}$$

$$H_1: \Delta \text{LDL } \textit{plantago ovata} - \Delta \text{LDL placebo} \geq |7.5| \text{ mg/dl}$$

Where  $\Delta \text{LDL} = \text{final LDL} - \text{baseline LDL}$

For a statistical significance of  $\alpha = 0.05$  and a power of 80%, with a standard deviation of 20 mg/dl in the  $\Delta \text{LDL}$ , the sample size required to detect significant differences of 7.5 mg/dl between the group treated with *Plantago ovata* and the group treated with placebo is 112 patients per group, for which, adjusted to an expected percentage of losses of 15%, a total of **270 patients** will be required.

After treatment, approximately 75% of the patients treated with soluble fibre (84 patients) and 85% of those treated with placebo (95) will not have 130 mg/dl of LDL-C in plasma. A statin will be added to all these patients' treatment.

It is assumed that the combination of soluble fibre with statins will cause the mean value of LDL-C to fall from 157 mg/dl to 125.6 mg/dl ( $\Delta \text{LDL}$  soluble fibre + statin = 31.4 mg/dl). In the placebo + statin group from 161 mg/dl to 136.85 mg/dl ( $\Delta \text{LDL}$  placebo+statin = 24.15 mg/dl).

For a statistical significance of ( $\alpha=0.05$ ), a power of 80%, a standard deviation in the  $\Delta \text{LDL}$  of 18.5 mg/dL and a ratio of 0.85 between groups treated with placebo for 0.75 treated with soluble fibre, **the sample size** necessary to detect differences of

7.25 mg/dl in the  $\Delta$ LDL between the group treated with statin+soluble fibre and the group treated with statin + placebo is 111 patients in the placebo group and 98 patients in the soluble fibre group.

As the percentage of failure in the objective of LDL-C equal to or lower than 130 mg/dl is 75% in the patients treated with soluble fibre and 85% in those treated with placebo, adding a 10% of patients lost to follow-up means that a **total sample of 290 patients (145 per group)** will be required.

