In clinical practice, in order to reduce cardiovascular risk, aside from the diet, many patients require treatment with cholesterol-lowering drugs, mainly statins. For this reason, it will be interesting to provide data on the effects of the statins in combination with the administration of soluble fibre. This approach is based on the different modes of action of both: whereas viscous fibre increases the loss of bile salts through the intestine, the statins, by means of the inhibition of 3-hydroxy-3-methylglutaryl coenzyme A reductase, reduce the synthesis of cholesterol. Nevertheless, it has yet to be demonstrated whether the combination of a soluble fibre- and statin-based drug provokes a synergistic additive effect, or whether, on the other hand, its cholesterol-lowering effects are neutralised. This study uses simvastatin, a regular and low-cost statin, which has a proven cholesterol-lowering additive effect with a fibre-rich diet. Simvastatin at a dose of 20 mg a day provides a 20-30% reduction in LDL-C.

Treatment with statins will be initiated in patients who fail to reach desirable concentrations of 130 mg/dl of LDL-C with soluble fibre, and it will thus be possible to study the effects of the combination of soluble fibre and statins.

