## **12.4. Analysis populations**

The statistical analysis will be performed both for intention to treat (each patient is analysed in the group he/she was assigned to at the beginning of the study regardless of whether he/she did not comply with the corresponding intervention) and by protocol, which only includes patients who complied suitably with the intervention that was assigned to them.

The safety analysis will include all the patients who received study medication; the adverse events in each treatment will be described graphically and/or numerically.

The Spanish version 11 of the statistical application package SPSS will be used for the data analysis.

A two-tailed significance of 0.05 will be considered in all statistical tests.

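### The statin-phase calculation that raises the sample from 270 to 290 uses a statin effect and a loss rate that conflict with the protocol's own figures, so its 80% power needs restating

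*Protocol*

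**What the plan says.** Protocol section 6.3 contains two calculations. The first, for fibre against placebo at week 8, needs 112 patients per group and is "adjusted to an expected percentage of losses of 15" per cent, which gives 270.

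The second concerns patients who have not reached the LDL-C goal at week 8 and receive a statin. It assumes that fibre + statin lowers mean LDL-C from 157 to 125.6 mg/dl (a change of 31.4). For the control it assumes "In the placebo + statin group from 161 mg/dl to 136.85 mg/dl" (a change of 24.15). The target is a difference of "7.25 mg/dl in the" change, with "a power of 80%, a standard deviation in the" change "of 18.5 mg/dL and a ratio of 0.85 between groups treated with placebo for 0.75 treated with soluble fibre". This needs 111 placebo and 98 fibre patients. The protocol divides by the shares expected to miss the goal (85% and 75%) and then, "adding a 10% of patients lost to follow-up means that a" total of 290 is reached.

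On the statin itself, section 4.1 states: "Simvastatin at a dose of 20 mg a day provides a 20-30% reduction in LDL-C". On test level, section 12.4 states: "A two-tailed significance of 0.05 will be considered in all statistical tests".

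**The concern.** Two inputs to the second calculation disagree with figures given elsewhere in the same protocol, and neither difference is explained.

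- **Statin effect.** The control arm is given a 15% fall on statin, below the bottom of the 20-30% range in 4.1. The fibre + statin arm, at 20%, only just reaches the bottom of the range quoted for the statin.
- **Losses.** Cumulative loss cannot be smaller at week 16 than at week 8, yet 6.3 uses 10% for the longer follow-up and 15% for the shorter. If the 10% is meant only for weeks 8 to 16, the losses before week 8 have been left out.

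This calculation is what moves the total from 270 to 290, and it is the only power statement for the fibre + statin objective. A result from that phase would be read against a claimed 80% power that the protocol's own figures do not support.

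**Working it through.** **Inputs.** Two-sided alpha 0.05 (12.4). From 6.3: SD of change 18.5 mg/dl, difference 7.25 mg/dl, placebo:fibre ratio 0.85:0.75, 145 per group, losses 10% and 15%. From 4.1: statin effect 20-30%.

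**1. Implied percentage falls.** Placebo + statin: 24.15/161 = 15.0%. Fibre + statin: 31.4/157 = 20.0%. The implied fibre increment is 5 percentage points.

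**2. The plan's own size and power.** With r = 0.75/0.85 = 0.882, the placebo n is (1 + 1/r) × [18.5 × (1.960 + 0.842)/7.25]² = 109.0, and the fibre n is 109.0 × 0.882 = 96.2. Rounded up this is 110 and 97; the protocol states 111 and 98, which agrees within one patient. Per group: 111/0.85/0.90 = 145.1 and 98/0.75/0.90 = 145.2, hence 145 and 290. At 111 and 98 the standard error is 18.5 × √(1/111 + 1/98) = 2.564 and 7.25/2.564 = 2.827. Power is 80.7% (normal) or 80.3% (t). The stated 80% and 290 therefore reproduce.

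**3. What the 10% covers.** Section 6.3 expects 84 fibre and 95 placebo patients to miss the goal. These are 0.75 × 112 = 84 and 0.85 × 112 = 95.2, so the shares are applied to the 112 who remain after week-8 losses. Working back from 111 and 98 to 145 leaves room for 10% loss in all.

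**4. Loss rate changed, difference kept at 7.25.**
- 15% cumulative: 145 × 0.85 × 0.85 = 104.8 placebo and 145 × 0.75 × 0.85 = 92.4 fibre. Standard error 2.640; power 78.4% (normal), 78.0% (t).
- 15% by week 8, then a further 10%: 94.3 and 83.2. Standard error 2.783; power 74.1% (normal), 73.6% (t).
- Size needed to hold the design at 15% loss: 111/0.85/0.85 = 153.6 and 98/0.75/0.85 = 153.7, so 154 per group, 308 in all.

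**5. Statin effect moved into the 20-30% range.** The result depends on how much fibre is assumed to add, which the documents do not give at that level. Three assumptions, with normal-approximation power at 290:

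| Assumption on fibre | Statin alone | Difference, mg/dl | Power, 10% loss | Power, 15% loss |
|---|---|---|---|---|
| Adds 5 percentage points | 20% | 0.25×157 − 0.20×161 = 7.05 | 78.5% | 76.1% |
| | 25% | 0.30×157 − 0.25×161 = 6.85 | 76.1% | 73.7% |
| | 30% | 0.35×157 − 0.30×161 = 6.65 | 73.6% | 71.2% |
| Multiplies remaining LDL-C by 0.80/0.85 | 20 / 25 / 30% | 6.59 / 5.93 / 5.26 | 72.8 / 63.7 / 53.7% | 70.4 / 61.2 / 51.4% |
| Scales the statin fall by 20/15 | 20 / 25 / 30% | 9.67 / 12.08 / 14.50 | 96% or more | 95.6% or more |

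**6. Week-8 primary comparison at 290.** 145 × 0.85 = 123 per arm. For 7.5 mg/dl and SD 20 the standard error is 20 × √(2/123) = 2.550 and 7.5/2.550 = 2.941. Power is 83.7% (normal), 83.4% (t).

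**The case against.** The best defence is that the calculation is internally correct: the protocol's inputs do give 80%. Power depends on the difference between the arms, not on the size of the statin effect itself, so a statin effect of 20-30% could lower or raise it. The loss discrepancy alone costs only about two points. The comparison is a secondary objective in 4.2, and 12.3.1 fixes the primary analysis as S8 against S0, although 8.1.1 words the primary endpoint loosely enough to include the statin phase. All of this stands, and it limits the point to an unsupported power statement for a secondary comparison.

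Stronger readings are tempting, but the documents do not support them:

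- **The planned contrast is about zero.** A reader might put 20% into the control arm and obtain 31.4 − 0.20 × 161 = −0.8 mg/dl. That raises only the control and leaves fibre + statin at 20%, so it sets the fibre increment to zero by assumption. Section 4.1 gives an effect for the statin and does not cap the combination at 20%.
- **True power is only about 19-24%.** That follows from comparing week-16 levels under equal percentage falls (4 × 0.8 = 3.2 or 4 × 0.7 = 2.8 mg/dl) with SD 18.5. But 18.5 is stated for the change, no SD for the level is given, and equal falls again assume no increment.
- **The sizing wrongly presupposes synergy.** Section 4.1 poses the combined effect as an open question and 6.3 labels its figures as assumed. Sizing on an effect not yet shown is normal practice.

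**Conclusion.** The point holds in limited form. The assumed 15% fall on placebo + statin conflicts with the 20-30% in 4.1, and 10% loss to week 16 conflicts with 15% loss by week 8. It would be wrong to say flatly that 80% is not delivered, because it is on the stated inputs; what fails is its support once the inputs agree with the rest of the protocol.

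Reconciling the losses alone brings power at 290 to about 78%, or about 74% if the 10% comes on top of the 15%. The second figure stacks two rates in a way the protocol never states. Moving the statin effect to 20-30% as well, at 15% loss, gives about 76% to 71%, provided the 5-point fibre increment is kept. That proviso is an assumption: across the three assumptions in the table, power at 15% loss runs from 51% to above 99%, so a range is the honest statement. The week-8 primary comparison is not harmed. This should be fixed, but it does not undermine the trial's main analysis.

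**What to change.** In section 6.3:

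1. Reconcile the assumed fall on placebo + statin with the 20-30% in 4.1, or give the reason for a lower figure, and state what fibre is assumed to add.
2. Use one cumulative loss rate to week 16, no lower than the 15% expected by week 8.
3. Restate the power of the secondary fibre + statin comparison at 290 as the resulting lower figure or range, with the assumption on the fibre increment named.
4. Justify 290 by the week-8 primary comparison: about 123 per arm after 15% loss, about 83% power for 7.5 mg/dl.

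The cost is a rewrite of the second half of 6.3 and a less favourable stated power. No extra patients are needed if the secondary power is restated. Holding 80% for the 7.25 mg/dl difference at 15% loss would take about 308 patients instead.
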